**3. PRELIMINARY STUDIES**

The concept of using a limited set of criteria to identify patients at risk of serious injury is not new to this study. In this section we will present our previous experience in developing selective criteria for computed head tomography in blunt trauma. The methodology used in our previous work is similar to the methodology developed for this proposal. This section also describes our candidate criteria and contains our sample size calculations.

**3.1 - Previous work on selective criteria.**

Phase I - Interrater Reliability

*Inter-rater Reliability of Criteria Used in Assessing Blunt Head Injury Patients for Intracranial Injuries*

[name], [name], [name], [name], [name] MD, [name], [name], PhD, [name], MA.

*Acad Emerg Med* 2003;10:830-5 [71].

Purpose: To determine the inter-rater variability of criteria used to evaluate blunt head injury victims for evidence of intracranial injury.

Methods: Physicians from 21 separate emergency departments performed paired evaluations of patients undergoing computed tomographic head imaging. Each physician independently determined whether each patient had any of the following characteristics: 1) eyes open spontaneously, 2) oriented, 3) follows commands, 4) seizure following trauma, 5) loss of consciousness, 6) prolonged loss of consciousness, 7) severe or progressive headache, 8) coagulopathy, 9) abnormal behavior, 10) abnormal level of alertness, 11) evidence of significant skull fracture, 12) persistent vomiting, 13) evidence of intoxication, 14) motor deficit, 15) gait abnormality, 16) abnormal cerebellar function, 17) cranial nerve abnormality, 18) inability to read or write, 19) presence of scalp hematoma, 20) neurological deficit. Responses were compared using the kappa statistic on a sample size of 3,951 patients, with a lower confidence value of 0.50 or greater interpreted to represent substantial inter-rater agreement.

Results: The physician evaluations exhibited the following kappa values: 1) eyes open spontaneously [Κ = 0.68], 2) oriented [Κ = 0.77], 3) follows commands [Κ = 0.76], 4) seizure following trauma [Κ = 0.42], 5) loss of consciousness [Κ = 0.82], 6) prolonged loss of consciousness [Κ = 0.71], 7) severe or progressive headache [Κ = 0.69], 8) coagulopathy [Κ = 0.73], 9) abnormal behavior [Κ = 0.64], 10) abnormal level of alertness [Κ = 0.66], 11) evidence of significant skull fracture [Κ = 0.62], 12) persistent vomiting [Κ = 0.66], 13) evidence of intoxication [Κ = 0.84], 14) motor deficit [Κ = 0.72], 15) gait abnormality [Κ = 0.77], 16) abnormal cerebellar function [Κ = 0.58], 17) cranial nerve abnormality [Κ = 0.69], 18) inability to read or write [Κ = 0.70], 19) presence of scalp hematomas [Κ = 0.68] 20) neurological deficit [Κ = 0.79].

Conclusions: We found substantial agreement between clinicians in their assessments of all criteria except the presence of seizure following injury.

Phase II - Derivation of Selective Criteria

*Developing a Decision Instrument to Guide Computed Tomographic Imaging of Blunt Head Injury Patients*

[name], PhD, [name], MA, [name], [name], [name], MD, [name]: NEXUS II Investigators.

*J Trauma* 2005;59:954-9 [74].

Purpose: To determine if a limited number of clinical criteria can reliably identify significant intracranial injuries in blunt trauma victims without missing any significant cases.

Methods: Clinicians assessed the presence or absence of candidate criteria on 13,728 consecutive blunt trauma patients for whom computed head tomography was ordered. Clinicians completed their assessments prior to obtaining imaging results. CT imaging results were reviewed to determine which patients had intracranial injuries. Recursive partitioning was used to identify which candidate criteria reliably predicted injury.

Results: The study enrolled 13,728 patients, including 917 with clinically important intracranial injuries. Recursive partitioning identified eight criteria that were highly associated with intra-cranial injury. These criteria include: 1 - evidence of significant skull fracture, 2 - scalp hematoma 3 - neurologic deficit, 4 - altered level of alertness, 5 - abnormal behavior 6 - persistent vomiting, 7 - coagulopathy, 8 - age 65 years or greater. This rule exhibits 98.3% sensitivity (C.I.: 97.2 – 99.0), a 99.1% negative predictive value (C.I.: 98.5 – 99.5), and a specificity of 13.7% (C.I.: 13.1 – 14.3). Implementation of this rule would have identified all but 16 of 917 patients having clinically important ICI, and would have correctly classified 1,752 (12.9%) patients as “low risk.” Follow-up evaluations, performed on 1,266 patients who did not undergo computed tomography during their initial presentations, reveal that a small minority of these patients ultimately receive cranial imaging. However, none of the follow-up cases required hospitalization or neurosurgical intervention, and there were no cases of missed intracranial injuries or death among this cohort.

Conclusions: We found that a limited number of clinical criteria can reliably identify significant intracranial injuries in blunt trauma victims. The optimal decision instrument developed in this project could still safely decrease tomographic imaging of blunt head injury victims by more than 12%.

Quality assurance reviews (comparing patients enrolled in the study against patients undergoing emergency computed head tomography) indicate that the clinicians are able to evaluate and enroll patients with 98% compliance. Discussions with site physicians and coordinators indicate that our data collection is simple and efficient, makes minimal demands on physicians, and is well tolerated in the clinical environment. Although we have the ability to terminate data collection at any site that is not compliant with protocols, we have had to take this action at only two institutions. Thus, most study sites have little difficulty implementing our protocols, and they are able to complete the evaluations in a timely and reliable fashion.

Our computerized data transfer and concatenation system is reliable and efficient. Computer problems occur infrequently and are usually corrected by remote reconfiguration of the problem computer. Rare hardware problems have been corrected by over-night transfer of redundant computers to serve affected sites until permanent hardware could be repaired. Data loss due to hardware and software problems has been limited to approximately a dozen cases.

**3.2 - Sample size calculations.**

To be clinically reliable, the combined selective criteria must satisfy two requirements. First, intracranial injuries requiring neurosurgical intervention must never occur in blunt head trauma victims identified as risk free by the instrument. This is equivalent to requiring a 100% negative predictive value. Second, every blunt trauma victim with a significant intracranial injury must exhibit at least one of the risk criteria. This requirement implies that the sensitivity of decision instrument be 100%.

Verifying negative predictive value and sensitivity at an absolute level is not statistically possible with a finite sample size. However, it is possible to estimate limits for the true values of these proportions using exact statistical relationships. The lower confidence limit of a proportion (such as negative predictive value or sensitivity) is related to the total size of the study population. The quantitative relationship is expressed by the following equation [48]:

[figure not shown]

Where:

P_L_ = Lower confidence limit for the proportion being studied (i.e. the lower confidence limit for the negative predictive value or sensitivity of selective criteria).

X = Number of times the event of interest is observed.

N = Total number of observations.

α = Statistical confidence value (Set to 0.05).

ν_1_ = Degrees of freedom for the numerator; ν_1_ = 2 [ N - X + 1 ]

ν_2_ = Degrees of freedom for the denominator; ν_2_ = 2 X

F_α/2,ν1,ν2_ = One tailed value of the F-distribution with ν_1_ and ν_2_ degrees of freedom.

Validating a given P_L_ to a 95% level of statistical certainty implies that α = 5% (or α = 0.05). The main hypothesis of this study states that selective criteria will detect all intracranial injuries requiring neurosurgical intervention in blunt head trauma victims without missing any such injuries. Thus, for purposes of sample size calculations, for either negative predictive value or sensitivity, the event of interest (presence of one of the risk criteria) should occur with every observation. Hence, X = N.

The degrees of freedom for the numerator and denominator are then given by:

ν_1_ = Degrees of freedom for the numerator; ν_1_ = 2 [ N - X + 1 ] = 2 [ N - N + 1 ] = 2

ν_2_ = Degrees of freedom for the denominator; ν_2_ = 2 X = 2 N

The expression for the lower confidence limit then becomes:

[figure not shown]

As discussed previously, practical concerns regarding radiographic charges and radiation health effects suggest that selective criteria will still remain cost effective and reduce mortality and morbidity even when missing 10 out of every 1,000 injuries. This implies that negative predictive value need only be verified to a 99.0% lower confidence level, or equivalently, P_L_ = 0.99. Substituting this value in the lower confidence limit equation yields the following algebraic equation for intracranial injury population size N;

[figure not shown]

The numerical solution to this equation is N = 368. Thus, to confirm that the decision instrument has a negative predictive value of at least 99.0%, the study must enroll 368 head injury victims who have none of the risk criteria, and none of whom have intracranial injuries requiring neurosurgical intervention. Since approximately 10% of head trauma victims are free of the risk criteria, this derivation would require a population of 3,680 head trauma victims. Unfortunately, confirming that the instrument has a 99.0% sensitivity requires studying 368 intracranial *injury* victims. Surgically significant intracranial injuries occur in only 1.2% to 1.4% of head trauma cases. Assuming a serious injury prevalence of 1.2% implies that this study will need to prospectively evaluate 31,000 blunt head injury victims. Consequently, study size is driven by the requirements of sensitivity.

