The monetary benefits derived from such a policy must be weighed against any excess morbidity incurred by patients who suffer neurologic consequences because of a failure to diagnose occult intracranial injury. There would be no cost if the negative predictive value of the low-yield criteria was 100% for lesions capable of producing neurologic injury. Alternatively, the utility of selective criteria would decrease with any decrease in the negative predictive value. If selective criteria had a true negative predictive value of 99.0%, then 10,000 blunt head injury victims would be inappropriately classified each year. As many as 1.4% of these cases could harbor intracranial injuries requiring neurosurgical intervention [65], therefore 140 intracranial injuries could be missed each year. Miller estimates that 23% of missed intracranial injuries produce neurologic sequelae [36], much lower numbers have been suggested in the British literature [52]. Taking the higher figure, selective criteria could annually miss up to 32 potentially preventable adverse outcomes. Severe disability or death associated with head injury results in lifetime costs of approximately $350,000 (including medical care, rehabilitation and lost wages) [53]. Assuming a worst-case scenario, where each missed injury results in death or severe disability, it is possible that $12 million would be needed to provide lifetime care for 32 such injuries. Thus, even with 99.0% negative predictive value, there could be annual dollar savings of over $75 million.

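### The 99.0% lower limit for negative predictive value is justified by a calculation that belongs to 99% sensitivity, so the NPV target is nearly uninformative and its savings claim is unsupported

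*Protocol*

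**What the plan says.** Section 3.2 names two requirements for clinical reliability, an NPV of 100% and a sensitivity of 100%, and relaxes both to a lower confidence limit of 99.0%. The reason given is that "selective criteria will still remain cost effective and reduce mortality and morbidity even when missing 10 out of every 1,000 injuries". The next sentence converts this to NPV: "This implies that negative predictive value need only be verified to a 99.0% lower confidence level". The NPV sample size follows: "the study must enroll 368 head injury victims who have none of the risk criteria, and none of whom have intracranial injuries requiring neurosurgical intervention". With about 10% of patients free of the criteria, that becomes 3,680 patients. The section then says that sensitivity drives the study size.

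The cost argument is in section 2: "If selective criteria had a true negative predictive value of 99.0%, then 10,000 blunt head injury victims would be inappropriately classified each year". It takes up to 1.4% of those 10,000 as neurosurgical injuries (140), 23% of these as having sequelae (32), and $350,000 for each (stated as $12 million). It concludes: "Thus, even with 99.0% negative predictive value, there could be annual dollar savings of over $75 million".

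Section 4.3.7 makes sensitivity for neurosurgical intervention the primary outcome and lists NPV among further characteristics. Section 4.3.7.2.1 uses sensitivity and NPV together to judge whether the instrument is reliable. Section 4.3.10.3 stops the study at 10 neurosurgical cases labelled low risk.

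**The concern.** Sensitivity and NPV have different denominators. Missing 10 of every 1,000 injuries is a statement about injured patients. An NPV error is a statement about patients labelled low risk, and each such error is already an injured patient. Section 2 applies the 1% error to all one million scanned patients instead of to the 10% to 12.9% who would be labelled low risk, and then multiplies by prevalence a second time.

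At stake are a stated performance threshold and the safety and cost case made for it. A reader would take 99.0% NPV to have been shown safe and cost-saving, when the calculation shows this for a different quantity. With an outcome this rare, a 99.0% NPV also says little about the instrument.

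**Working it through.** **Inputs.** Section 2: 1,000,000 scans a year; $750 per scan; 12.9% reduction in imaging; prevalence 1.2% to 1.4%; 23% of missed injuries with sequelae; $350,000 per adverse outcome. Section 3.2: about 10% free of the criteria; α = 0.05 with α/2 in the lower tail; 31,000 patients.

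**1. The protocol's figures reproduce.** With no misses the exact lower limit is 0.025^(1/N). Setting it to 0.99 gives N = ln 0.025 / ln 0.99 = 367.04, so 368. Then 368/0.10 = 3,680, and 368/0.012 = 30,667, stated as 31,000. Cost chain: 1,000,000 × 0.01 = 10,000; × 0.014 = 140; × 0.23 = 32; × $350,000 = about $11.3 million (stated as $12 million); $90 million − $12 million = $78 million.

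**2. What the 140 is.** Injuries a year at 1.4% are 14,000, and 1% of 14,000 = 140. This is the number missed at 99% sensitivity.

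**3. What 99.0% NPV implies on the same inputs.**

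| | 10% low risk | 12.9% low risk |
|---|---|---|
| Low-risk patients a year | 100,000 | 129,000 |
| Missed injuries (1%) | 1,000 | 1,290 |
| Adverse outcomes (23%) | 230 | 297 |
| Cost at $350,000 | $80.5M | $103.8M |
| Charges avoided at $750 | $75.0M | $96.75M |
| Net | −$5.5M | −$7.1M |

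Per low-risk patient: 0.01 × 0.23 × $350,000 = $805 lost against $750 saved. Break-even NPV is 1 − 750/(0.23 × 350,000) = 99.07%. At 99.0% NPV, the break-even share with sequelae is 750/(0.01 × 350,000) = 21.4%.

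**4. How demanding the limit is.** A test with no information has NPV = 1 − prevalence = 98.6% to 98.8%. Sensitivity at 99.0% NPV is 1 − 0.01 × (low-risk share)/(prevalence), from 1 − 0.00129/0.012 = 89.3% to 1 − 0.001/0.014 = 92.9%. Conversely, 99% sensitivity corresponds to NPV = 1 − 0.01 × (prevalence)/(low-risk share), from 1 − 0.00014/0.10 = 99.86% to 1 − 0.00012/0.129 = 99.91%.

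**5. The criterion at the planned size.** Of 31,000 patients, 3,100 (10%) to 3,999 (12.9%) would be low risk. Exact lower limits for NPV:

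| Misses | 3,100 low risk | 3,999 low risk |
|---|---|---|
| 0 | 99.88% | 99.91% |
| 9 | 99.4% | 99.6% |
| 10 | 99.4% | 99.5% |

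The limit stays at or above 99.0% for up to 20 misses (3,100) or 27 misses (3,999). The study stops at 10. With 9 misses among 368 cases, the exact lower limit for sensitivity is 95.4%, far below its own 99.0% target, while NPV still passes.

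**The case against.** **The error does not reach the study's main conclusion.** This stands. Sensitivity is primary and sets the size, its 99.0% limit matches the 140-miss calculation, and section 3.2 requires both criteria. A reader might infer that an instrument missing 20 to 27 neurosurgical cases could be declared validated. The documents do not support that: the study would have stopped at 10, and the sensitivity criterion would already have failed. What remains is that, at the planned size, the NPV criterion cannot fail before the stop and so adds nothing, although it is presented as a joint requirement.

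**The net loss is fragile.** This also stands. A reader might infer that 99.0% NPV definitely loses money. The gap is $805 against $750 on rounded inputs. Section 2 describes 23% as the higher figure, says that much lower ones exist, and calls its costing a worst case. Below 21.4% with sequelae the sign reverses. The supportable statement is that a saving of over $75 million does not follow. The seven- to nine-fold undercount of misses depends on neither the 23% nor the $350,000.

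**A broader outcome might rescue the calculation.** If NPV referred to any clinically important injury (917/13,728 = 6.7% in the derivation study), neurosurgical cases would be about 18% to 21% of misses (1.2/6.7 to 1.4/6.7). At 12.9% low risk the cost would be about $19 to $22 million and there would be no loss. But section 3.2 defines its NPV on injuries requiring neurosurgical intervention.

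**A tempting replacement limit.** Charging $350,000 for every miss gives a break-even of 1 − 750/350,000 = 99.79%, which suggests a limit of 99.8%. That drops the protocol's 23% and so does not follow from its own costs. It would also still be looser than the 99% sensitivity target.

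**Conclusion.** The concern holds for the justification and level of the NPV target, with moderate severity. Sections 2 and 3.2 present a 99% sensitivity calculation as support for a 99.0% NPV limit. On the protocol's inputs, 99.0% NPV for neurosurgical injury means 1,000 to 1,290 missed injuries and 230 to 297 adverse outcomes a year, not 140 and 32, and roughly no saving or a small loss. The loss requires more than 21.4% of missed injuries to have sequelae. The health argument weakens too: section 2 sets 5 prevented malignancies against 32 adverse outcomes, and at 99.0% NPV the comparison is with 230 to 297.

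The arithmetic giving N = 368 is correct. The 368 cases, the 31,000 patients, the stopping rule and the primary analysis stand. These results rest on the stated prevalence of 1.2% to 1.4% and low-risk share of 10% to 12.9%.

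**What to change.** In sections 2 and 3.2:

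- Attach the 99.0% limit and the chain of 140 misses, 32 outcomes and $12 million to sensitivity only.
- Delete the savings claim at 99.0% NPV.
- Withdraw the 99.0% NPV target and its sample size of 368 low-risk patients (3,680 in total).
- Then either report NPV with its exact interval and no threshold, or set a limit consistent with 99% sensitivity, about 99.86% to 99.91% depending on prevalence and low-risk share. Amend the joint requirement in sections 3.2 and 4.3.7.2.1 to match.

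This changes wording only. No extra patients are needed: 3,100 to 3,999 low-risk patients with no miss give lower limits of 99.88% to 99.91%. The price is a less favourable stated NPV and savings case and, if a limit is set, a stricter NPV requirement with almost no room for a miss.

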**4. EXPERIMENTAL DESIGN AND METHODS**

**4.1 - Experimental Design**

The study will be conducted as a multicenter prospective evaluation of blunt head trauma patients undergoing computed head tomography. Participating study centers encompass a range of acute care facilities including academic trauma centers, community trauma centers and community emergency departments. Surveying a wide range of hospitals will make the study results generalizeable the majority of mild head injury victims.

The study will use an experimental design similar to that implemented in the previous study *Selective Computed Head Tomography in Blunt Trauma* (PHS Grant No. R01 HS09699). This computed tomographic derivation study is particularly important to the current proposal because it has already evaluated the use of a multicenter network needed to conduct the blunt head injury validation research. In addition, both studies use very similar methodology and protocols. Thus, the core methodology for evaluating blunt head injuries has already been tested in the derivation study. Personnel trained for the earlier study have become experienced with this methodology and can be quickly updated to the new protocols needed for the validation study. Most importantly, the derivation study demonstrates that the methodology for the current proposal is feasible and can be conducted in the clinical environment. The derivation study involved over 800 physicians, as well as a similar number of supporting technicians and nurses, working at 21 institutions, and accumulated over 600 cases per month.

